## Abstract

**Background:**

*On the Road to Recovery* (OTRTR) is a brief low intensity group psychological therapy that aims to improve patients’ insight into their mental disorder and develop adaptive coping skills to help manage distress. OTRTR is currently delivered in forensic mental health services in Scotland. However, to date, this therapy has not been evaluated as to its effectiveness or safety for forensic patients.

**Methods:**

This is a parallel-group feasibility randomized controlled trial with single-blind assessments comparing OTRTR therapy to treatment as usual (TAU) for forensic mental health patients. Fifty participants will be recruited from high, medium, and low secure forensic mental health services in Scotland. Participants will receive OTRTR for approximately 12 weeks or continue treatment as usual for 12 weeks. The trial’s primary aims relate to testing the acceptability and feasibility of key trial procedures that would be necessary for a definitive RCT of OTRTR. The secondary aims include estimating therapeutic effect sizes on clinical outcomes including insight and coping skills. The study design also features an adverse event monitoring plan to estimate the safety of OTRTR for participants, as well as use of intensive longitudinal methods to identify “key ingredients” to the OTRTR therapy protocol.

**Discussion:**

This study will inform the design and sample size for a future full-scale randomized controlled trial (RCT), which will be conducted to determine the effectiveness of the *On the Road to Recovery* intervention in improving forensic mental health patients’ clinical insight and coping skills.

**Trial registration:**

ISRCTN Registry, ISRCTN75126867 registered 27 July 2017

## Background

Forensic mental health patients often present with varied and complex treatment needs relating to their mental health and offending behavior [1, 2]. Treating these individuals requires significant involvement of clinical and forensic psychological practitioners as part of the multi-disciplinary treatment team. However, the evidence base for psychological interventions with forensic patients remains severely limited. Previous reviews have highlighted that a lack of rigorous methodologies, including the randomized controlled design, in forensic mental health evaluations has restricted the synthesis of effectiveness evidence in this field [2, 3].

Within NHS Scotland, psychological treatment of forensic patients is guided by the Forensic Matrix (an addendum to the larger “Matrix,” a guide to delivering evidence-based psychological therapies in Scotland [4]). The Forensic Matrix proposed a model of “stepped care” [5] for forensic patients. This model acknowledges that forensic patients often present with complex and enduring problems relating to their risk and offending behaviors which require highly specialist and individually tailored psychological treatment from practitioners with high levels of training and forensic expertise. However, they often also have simpler underlying or associated psychological needs which may respond to less intensive interventions. According to the Forensic Matrix stepped care approach, different levels of intervention intensity can be used to address forensic patients’ needs. For example, a forensic patient may require psychological work aimed at improving their management of basic emotions (low intensity) before the patient will be able to cope with the demands of sex-offending treatment (specialist/highly specialist). Several psychological interventions which address different common underlying needs of forensic patients have now been developed as part of the Forensic Matrix suite of interventions. There is now a critical need to evaluate the effectiveness of these therapies.

*On the Road to Recovery* (OTRTR) is a brief, low intensity group psychological intervention delivered across the Scottish Forensic Mental Health Managed Care Network (“Forensic Network”). The OTRTR protocol was written in 2011 by a working group of clinical and forensic psychologists within the Forensic Network. The program is based on the principles of cognitive behavior therapy with a focus on compassionate mind training [6]. The core purpose of OTRTR is to open a dialog about recovery and instill in patients hope that recovery is possible. It is intended to be one of the first psychological treatments offered to patients on their journey to recovery from mental health difficulties, prior to engaging in more demanding and longer term therapy.

The aim of this study is to determine the feasibility of conducting an RCT comparing *On the Road to Recovery* psychological therapy to treatment as usual (TAU) for forensic mental health patients. Consistent with the UK Medical Research Council guidance (MRC) results from this study will directly inform the decision to undertake a future definitive RCT of OTRTR [4, 5]. Specifically, the feasibility RCT will determine:Participant recruitment, consent, and retention ratesAcceptability of randomization to treatment conditionAcceptability of the OTRTR intervention for patientsSafety of the OTRTR intervention for patientsAcceptability of intensive longitudinal modeling procedures, in terms of:The completion rate of standardized recording forms of the therapy content delivered by OTRTR therapy facilitatorsThe completion rate of primary clinical outcome measures weekly during treatment phaseObtain estimates of likely therapeutic effects of OTRTR for use in sample size calculation of a future definitive trial. The between-group mean difference in therapeutic outcomes at the post treatment assessment, along with the standard deviation of the outcome for the entire sample, at baseline will be recorded.

## Methods

### Design

This study is a feasibility study using a parallel-group randomized outcome blinded design to compare OTRTR to treatment as usual (TAU). As a feasibility study, the primary study aims relate to testing the acceptability and feasibility of key trial procedures that would be necessary for a full-scale RCT of this program. The comparator group will receive treatment as usual. In this study, 50% of participants will be randomized to commence OTRTR immediately for approximately 12 weeks. The remaining 50% will engage in TAU for 12 weeks and may complete OTRTR in the future. Participants will continue their usual access to concomitant therapies and therapeutic activities throughout the study. Participants will complete a range of self-report measures and a clinical interview at baseline (T0), post treatment (T1), and at follow-up (T2), 3-months after the T1 assessment, with an assessor who will be blind to participants’ allocation status. Clinical effect sizes will be estimated using two approaches, at the group level for a range of clinical outcomes by comparing change from pre to post treatment and at the individual level for the two primary outcomes—insight into mental disorder and use of adaptive coping skills—using intensive longitudinal methods (ILM) [7, 8]. Findings from two large treatment evaluations, the PEPS trial [9] and Ministry of Justice’s evaluation of the prison-based Core Sex Offender Treatment Programme [10], demonstrated that psychological therapies have the potential to cause harm to patients, a concept which has received little attention until recently. Accordingly, this study will pilot an adverse event monitoring plan to estimate the safety of OTRTR for participants.

Following participation in the study, participants will be offered the opportunity to complete a semi-structured interview which will gather qualitative information on their experiences of participating and views on different aspects of the trial (for instance, randomization, treatment, and assessments).

### Study setting

Participants will be recruited and identified from forensic mental health services which are part of the NHS Scotland. Services include high, medium, and low secure inpatient settings as well as community forensic teams.

### Sample size

As this study is a feasibility trial, a power calculation to determine sample size was not undertaken [11]. The target recruitment for this feasibility trial will be *N* = 50 (25 in each intervention arm). This figure is consistent with recommendations for pilot and feasibility studies and appropriate given the study aims [12, 13].

### Inclusion criteria

People meeting inclusion criteria for the study include (1) males and females aged between 18 to 65 years, (2) who are receiving treatment under the Mental Health (Care and Treatment) (Scotland) Act 2003 from a participating forensic mental health service, and (3) who are viewed by their Responsible Medical Officer (RMO) as capable of providing informed consent and well enough to participate in the study.

### Exclusion criteria

People meeting exclusion criteria for the study include (1) those with a diagnosis of intellectual disability, (2) those who are viewed by their RMO as incapable of providing consent or are too unwell to participate, and (3) those who have completed *On the Road to Recovery* in the prior 3 years.

### Identification and recruitment of participants

The study inclusion criteria were selected to match the broad range who are referred to On the Road to Recovery. Potential participants will be identified by their local psychological therapies team using the existing local referral process. The Responsible Medical Officers for each patient referred to On the Road to Recovery will be consulted on whether their patient has capacity to provide informed consent. Those without capacity will not be approached about the research. Potential participants with capacity to consent will be first informed of the study by their local psychological therapies team. Subsequently, a researcher will meet with these potential participants that have expressed an interest to provide them with further information and obtained informed consent to participate.

#### Implementation

Staff of the Forensic Network office will generate the allocation sequence using an online randomization service (www.sealedenvelope.com). The Forensic Network office provides a centralized staff group who are knowledgeable of the participating services (the potential participating sites are part of the “Forensic Network”) but also independent from the trial research team. The Forensic Network office will generate the allocation sequences using an online randomization service (www.sealedenvelope.com). The researcher completing the baseline assessment will communicate the information necessary for allocation (site and assessed treatment need) to the Forensic Network office within 3 days of the participants’ T0 assessment. The Forensic Network office will allocate the participant and relay this information to the local investigators by email and keep a randomization record to audit compliance with the randomization procedure.

### Blinding

The assessor administering measures at T0, T1, and T2 assessments will be blind to participants’ allocation status. Participants and OTRTR facilitators will not be blind to allocation status. Participants will be asked not to divulge information about their group to the assessor. Any instances of unblinding will be recorded, and the clinical outcome analysis will be repeated excluding these participants to determine the robustness of the findings.

### Description of the intervention

#### On the Road to Recovery

The OTRTR program is comprised of two brief treatment modules: *Awareness & Recovery* (A&R) and *Looking After Yourself* (LAY). A&R provides psychoeducational material adapted from Morrison et al. [16] “Think you’re crazy? Think Again” and from “Coping with Mental Illness” [17], the original psychoeducation program delivered across the Forensic Network. The LAY program’s core aim is to help patients develop basic coping skills to manage psychological distress and to develop a “toolkit” for coping with this distress now and in the future. The protocol is semi-structured and organized by topics instead of sessions, which allows the program to flexibly match pace to groups with greater or lesser need by adjusting the number of sessions. Each topic contains several objectives that are accompanied by structured didactic activities, exercises, and discussion prompts. The program will run over approximately 12 weeks, with weekly 2-h sessions. Treatment delivery is primarily in small groups; however, the program can also be delivered on an individual basis as part of the study. Participant attendance and engagement in the treatment sessions will be monitored and recorded. Participants’ RMOs may withdraw a participant from the study and therefore discontinue OTRTR sessions should there be a deterioration in participants’ clinical presentation.

OTRTR therapy facilitators will receive group supervision at least once every four sessions delivered, consistent with the Forensic Matrix governance standards [18]. Facilitators will be provided with standardized recording documents to closely record the program content delivered in each session.

#### Treatment as usual

Participants randomized to the TAU condition will engage in treatment as usual including access to other psychological therapies, with the exception that they do not attend OTRTR sessions. TAU participants will be advised they will be offered the OTRTR therapy at a later stage. Access to and engagement in non-psychological therapies differs by participating site and individual participants. For both groups, we will record the care received by participants during the trial to enable a full description of treatment as usual.

### Safety monitoring

We will monitor potential harm from study treatments experienced by participants by recording the occurrence of adverse (AE) and serious adverse events (SAE). Any AE and SAE experienced by participants after consenting to the study will be recorded and reported regardless of whether it is likely that they are the result of treatment received. The Health Research Authority defines SAE as an occurrence that (a) results in death, (b) is life-threatening, (c) requires hospitalization or prolongation of existing hospitalization, (d) results in persistent or significant disability or incapacity, and (e) consists of a congenital anomaly or birth defect. Applying this definition to psychiatric inpatient settings, acts of serious self-harm, attempted suicide, and suicide would qualify as a SAE. Events that constitute SAEs are already routinely collected and monitored at all participating sites using the Datix incident reporting software.

AEs will be similarly monitored throughout the study. In the present study, an AE is considered to have occurred if either of the following takes place: (a) participant is removed from the study at the request of their RMO due to significant deterioration in the patient’s mental state and/or behavior and (b) a participant’s global CORE-OM score (indexes overall psychiatric distress) increases from the previous assessment to an extent that is both clinically significant and reliable (as defined in Evans et al. [19]). All SAEs and AEs will be recorded, and SAEs will be reported to a NHS Scotland Research Ethics Committee if and when they occur.

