#### Primary outcome measures

Primary study outcomes relate to the feasibility and acceptability of key trial procedures.Number of eligible participants identified over the study period will be indexed by the total number of participants identified across sites who meet eligibility criteria.Estimate rate of recruitment into the trialThe proportion of eligible patients who agree to participate (provide consent): We anticipate the consent refusal rate to fall in the range of 16–37% based on findings from previous RCTs of psychological interventions in forensic populations [21–24]. The adopted benchmark of success in this study is a consent refusal rate in this study of less than 37%.The number of participants enrolled into the study each month during the recruitment period: As in other ongoing feasibility RCTs [25], the benchmark of recruitment success is achieving 80% of target sample size, in this case recruiting at least 40 participants into the study.Audit adherence to randomization procedure: The number of instances where the actual treatment allocation differed from assigned allocation. Instances where the participant is removed from the study by his or her RMO, who cites a reason related to the allocated condition as opposed to deterioration in clinical presentation, will also be considered non-adherence to the randomization process. Any instances of non-adherence to the randomization procedure will cause great concern as to the feasibility of a future phase III RCT of OTRTR.Estimate completion rate of OTRTR: Proportion of participants who complete OTRTR. Following similar studies [26, 27] participants will be considered to have completed OTRTR if they attended at least 80% of the planned sessions.Explore reasons for study drop-out during the study treatment: Participants will have the option of providing a reason they do not wish to continue with the study before exiting the study.Completion rate of primary clinical outcome measures weekly during treatment phase: The proportion of Birchwood Insight Scale (BIS) and Coping Styles Questionnaire (CSQ) forms completed as intended each week during the treatment phase will be calculated.Completion rate of standardized recording forms of the therapy content delivered by OTRTR therapy facilitators: Proportion of complete forms will be calculated.Number of participants lost to follow-up and reasons: Number of participants who withdrew from the study or who were otherwise lost to follow-up, with reasons recorded (if provided). The adopted benchmark of success is a participant attrition rate of less than 20% at the post-treatment (T1) assessment.Safety of OTRTR for patients: Descriptive statistics for frequency of observed AEs and SAEs across treatment conditions. Adverse events may occur for reasons independent of the therapy being studied due to the nature of this clinical population. Safety of OTRTR will be assessed by comparing the rates of SAEs and AEs across the two study treatment conditions. We will also compare the incident rate of SAEs for study participants to the rate observed for each participant in the 12 weeks prior to enrolment in the study. This reference data will be requested from the local site clinical effectiveness departments or equivalents following study completion.Average duration of assessment battery at T0, T1, and T2. Descriptive statistics for length of assessment. We anticipate the T0 assessment will last approximately 90 min, and the T1 and T2 assessments 60 min each.

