### Participant and data retention

Participants may withdraw from the study at any time. We will offer participants who choose to withdraw from the study the opportunity to share their views and reasons for withdrawal in a post-study interview at the time of their exit from the study. Participants will be reassured that this is voluntary, and they need have no further contact with the research team. Discontinuing OTRTR therapy will not exclude participants from the study. Participants who wish to discontinue OTRTR will be offered the opportunity to participate in the regular assessment points should they wish. Participants who withdraw from the research study will be able to continue (if in OTRTR condition) or commence (if in TAU condition) OTRTR in the context of their usual care and treatment. Measures will be clearly prioritized so that in all assessment batteries primary measures will be administered prior to secondary minimizing the loss of primary data should participants withdraw during an assessment session. The assessment battery may be completed over two sessions to avoid participant testing fatigue.

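### The adverse-event definition is narrow for a safety outcome compared between arms: it can leave a substantial share of reliable CORE-OM worsening uncounted, and its removal criterion is open to differential ascertainment

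*Protocol article*

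**What the plan says.** All references are to the protocol article.

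- **Scope (Safety monitoring).** AEs are recorded from consent regardless of cause, but the definition is closed: "an AE is considered to have occurred if either of the following takes place".
- **Criterion (a).** The "participant is removed from the study at the request of their RMO due to significant deterioration" in mental state and/or behaviour.
- **Criterion (b).** The global CORE-OM score "increases from the previous assessment to an extent that is both clinically significant and reliable". The meaning of those terms is left to a cited source. CORE-OM is taken at T0, T1 and T2 in both arms (Table 1).
- **Use (Primary outcome measures).** "Safety of OTRTR will be assessed by comparing the rates of SAEs and AEs across the two study treatment conditions". Serious adverse events (SAEs) are captured separately through routine incident reporting.
- **Removal and treatment (On the Road to Recovery).** "RMOs may withdraw a participant from the study and therefore discontinue OTRTR sessions should there be a deterioration" in clinical presentation.
- **Treatment and study status (Participant and data retention).** "Discontinuing OTRTR therapy will not exclude participants from the study". The same section says that people who withdraw from the research may carry on with OTRTR as part of usual care.
- **Blinding.** The assessor is blinded; participants and facilitators are not. Nothing is said about RMOs.

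**The concern.** Possible harm from psychological therapy is part of the stated rationale, and safety is a listed primary outcome. Because the AE definition is closed, it is the measuring instrument for the AE part of that outcome. It has two weaknesses.

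Criterion (b) joins two conditions and looks back only one assessment, so it can count no more than a subset of reliable worsening.

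Criterion (a) needs a management act as well as deterioration. If RMOs remove deteriorating patients more readily in one arm than in the other, the AE rates will differ even when deterioration does not. At stake are a thin AE count, a between-arm contrast partly shaped by removal decisions, and a definitive trial that inherits the same definition.

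**Working it through.** The protocol gives no AE rate, CORE-OM cut-off, reliable-change value, SD or baseline distribution, so there is no planned figure to reproduce. The figures below are illustrations on assumed inputs.

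**1. Criterion (b): how much reliable worsening the conjunction leaves out**

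Model, in SD units: previous score x ~ N(0, 1); next score y = ρx + √(1 − ρ²)·e + m, with e ~ N(0, 1); cut-off c set so that a share q of participants starts above it. There were 1,000,000 draws per scenario.

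- Reliable worsening: y − x > RC, with RC = 1.96·√(2(1 − reliability)).
  - Reliability 0.80: 1.96·√0.40 = 1.240
  - Reliability 0.90: 1.96·√0.20 = 0.877
  - Reliability 0.94: 1.96·√0.12 = 0.679
- Counted under (b), reading clinical significance as crossing the cut-off: also x < c ≤ y.
- Assumed (reliability, ρ) pairs: (0.90, 0.7), (0.94, 0.7), (0.90, 0.5), (0.80, 0.6). Mean worsening m: 0 or 0.3. q: eight values from 10% to 90%. This makes 4 × 2 × 8 = 64 scenarios.

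Share of reliable worsening not counted (lowest and highest over the eight combinations of reliability, ρ and m):

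| Already above cut-off | Not counted |
|---|---|
| 10% | 0.639–0.807 |
| 30% | 0.391–0.612 |
| 50% | 0.359–0.555 |
| 70% | 0.440–0.627 |
| 90% | 0.702–0.830 |

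The overall range is 0.359 to 0.830. The share exceeds one half in 49 of the 64 scenarios, three of them by 0.002 or less.

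The loss has two sources. With reliability 0.90, ρ = 0.7, m = 0 and q = 50%, the uncounted 0.502 splits into 0.253 already above the cut-off and 0.249 worsening but staying below it. With q = 90% nearly all of it (0.757 of 0.776) is in people already above.

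Per interval, 0.082–0.313 of participants worsen reliably (25 × 0.082 ≈ 2 to 25 × 0.313 ≈ 8 per arm). Under the conjunction it is 0.024–0.165 (25 × 0.024 = 0.6 to 25 × 0.165 ≈ 4 per arm).

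A separate simulation with ρ = 0.7, a threshold of 0.6–0.8 SD and 30–70% above the cut-off gave 0.365–0.478 counted, so about 52–63% uncounted.

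**2. Criterion (b): the one-step comparison**

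With RC = 0.877 SD, rises of 0.6 SD from T0 to T1 and 0.6 SD from T1 to T2 total 1.2 SD. The total exceeds RC but neither step does, so no AE is recorded. This needs no assumption about the cut-off.

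**3. Criterion (a): differential removal**

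Expected AEs per arm = 25 × P(deterioration) × P(removal | deterioration). Take 20% deterioration in both arms:

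- Removal 0.50 in both: 25 × 0.20 × 0.50 = 2.5 vs 2.5, ratio 1.0.
- Removal 0.50 vs 0.25: 2.5 vs 25 × 0.20 × 0.25 = 1.25, ratio 2.0.
- Removal 0.60 vs 0.10: 3.0 vs 0.5, ratio 6.0.

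The ratio equals the ratio of removal probabilities. The protocol gives no information on those probabilities.

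**4. The sections on removal and treatment**

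The intervention section presents the end of OTRTR sessions as a consequence of withdrawal by the RMO. The retention section lets sessions stop without leaving the study, and lets someone leave the study and keep attending. The second may be meant for withdrawal by the participant only, but the text does not say so.

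**The case against.** The case for the plan is substantial, and most of it stands as a limit on the point.

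- **Criterion (a) is not removal instead of deterioration.** It requires removal because of deterioration, and (b) counts worsening without removal. This stands. The weakness is only that removal is needed in addition.
- **A reader might infer that the whole AE comparison is asymmetric.** The documents do not support that. Both criteria apply to both arms, and CORE-OM follows the same schedule with a blinded assessor. OTRTR can be stopped without leaving the study, so removal is not the only route, and an RMO could also remove a deteriorating TAU patient. What remains is a risk in (a), of unknown size.
- **A reader might infer that most reliable worsening is missed.** That is not shown. The definition is in a source not at hand, and the assumed range starts at 36%.
- **A reader might infer that anyone above the cut-off at T0 can never register an AE.** This is wrong even on the cut-off reading. They can register under (a), or under (b) by falling below at T1 and rising above again by T2. Only those who remain above are shut out of (b).
- **Worsening is visible elsewhere.** The Clinical outcomes analysis plans reliable change indices, SAEs are captured separately, and BPRS, violent incidents and withdrawals are all recorded. The AE comparison is therefore not unreadable. But none of these enters the AE rates that the protocol compares.
- **This is a descriptive pilot.** With 25 per arm and no progression criterion based on AEs, a strict threshold can be defended as limiting false alarms. That is a reason to keep the strict count visible, not to report it alone.
- **Recording RMO-judged deterioration does not remove the bias.** It remains a judgement by a treating doctor for whom no blinding is stated. This stands and should be acknowledged.

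**Conclusion.** The point holds in a limited form. The AE definition is narrow for an outcome compared between arms. Criterion (b) can count only a subset of reliable CORE-OM worsening, and it misses worsening that accumulates in steps below the threshold; both follow from the wording. The size does not. If clinical significance means crossing a cut-off, roughly 36–83% of reliable worsening within an interval goes uncounted, depending on the share above the cut-off at baseline, the reliability and retest correlation of the measure, and the mean shift, all of which are assumed.

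Criterion (a) is open to differential ascertainment because it depends on removal by an RMO for whom no blinding is stated, and because removal is tied to stopping OTRTR. The protocol fixes neither the size nor the direction of any resulting difference.

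This is a cheap improvement to the measurement of safety, not a flaw that makes the safety data uninterpretable.

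**What to change.** 1. In the AE table, report by arm every reliable CORE-OM increase, judged against both T0 and the previous assessment and irrespective of the cut-off. Keep the current rule (reliable and clinically significant) as a separate row.
2. Record RMO-judged significant deterioration in both arms over the same period, whether or not the participant leaves the study. Show RMO removals as a separate row, and state that the judgement is unblinded.
3. Reconcile the On the Road to Recovery and Participant and data retention sections on whether leaving the study stops OTRTR. Which rule should apply is for the trial team.

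**Cost.** Item 1 needs only scoring of data already collected. Item 2 adds one recorded item per participant. AE counts will rise in both arms: in the scenarios with no average worsening, 0.082–0.191 of participants still worsen reliably per interval, about 2 to 5 of 25. The broader row should be read against that background and beside the stricter one.
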